#### Group and Individual Consultations (Group III)

For group III, the intervention program will also include a single group consultation of 60 minutes led by a nurse and a pharmacist followed by two individual consultations of 30 minutes with a nurse.

During the group consultations patients receive information about their disease, cardiovascular medication (statins and antihypertensive and antithrombotic agents), and the importance of treatment adherence. Patients will receive an information booklet with all information presented during the plenary session. At the end of this consultation patients are asked to keep a diary of their medication intake during a 2-week period and to set a personal goal for the upcoming individual consultation with a nurse. The group consultation is regarded as an efficient way to increase knowledge and understanding of the risks. It also provides a gathering with other patients (peers).

During individual consultations, the intervention is further tailored based on the goal previously set, patient’s concerns, and necessities using the results of the screening questionnaire (see Data Collection). The following topics will be discussed during the individual consultation: patient's motivation and confidence (barriers, concerns, and positive self-motivational statements about their adherence behavior), options for increasing adherence to treatment, and a global summary of the counseling session.

Both the group and the individual consultations take place at the outpatient clinic. The involved nurses have had training in motivational interviewing [21] and were especially trained for this intervention by a psychologist.

For each of the constructs, we used the recommended behavior change strategies [12,13]. We tailored the intervention further by using the taxonomy of Abraham and Michie [22,23] and the coding manual by de Bruin [24] to categorize the behavior change techniques to be included in the intervention. For each of the components of HBM, the determinants, techniques, and application strategy were developed and are detailed in Figure 1-4.

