### Assignment of Interventions

Patients who meet the criteria and consent to participate will then be randomized by the nurse stratified by department (eg, neurology, vascular surgery, and cardiology) in a 1:1:1 ratio into one of the three groups using computer randomization.

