### Statistical Methods

The data will be analyzed based on the intention‐to‐treat principle and evaluated using SPSS, with descriptive statistics (mean, median, SD, and interquartile range) being determined for all variables. The data will be presented in quantitative format (eg, biometrics, laboratory results, blood pressure, lifestyle scores, adherence score on the basis of refill data, and the MMS) and in descriptions of observed effects (eg, change in BMQ, determinants for adherence, evaluation of the use of iVAZ, and appreciation of nurse intervention).

To evaluate the difference between the groups, an analysis of variance test will be performed on the outcome measures for the three patient groups. The independent variable will be the three intervention groups. The dependent variable is medication adherence measured with the dedicated calculation of refill data. Specifically, we will compare the difference between the first and last time-point between groups for the primary and secondary outcomes measures. For the intervention groups II and III, we will also compare the outcomes of the clinical data at 16 and 28 weeks. To correct for multiple comparison, a Duncan’s multiple range test will be performed. Furthermore, we will perform a receiver operating characteristic (ROC) curve analysis to compare the outcome of the screening instruments (MMS and BMQ) with the pharmacy refill dates. In the ROC curve plot, specificity of the questionnaire is on the x-axis and sensitivity of the question is on the y-axis.

Plausible relations between parameters of cardiovascular risk factors, motivation to change, socioeconomic class, and parameters of adherence (calculated refill score and BMQ and MMS scores) will be tested in a univariate manner. Individual parameters will be tested for normality using the Kolomogorov-Smirnov test in order to select adequate univariate tests. Multiple logistic regression analysis will be performed to assess the relative importance of selected parameters for the likelihood of low adherence, as defined by the refill data algorithm. In all analyses, potential confounders will be included if they independently changed the beta coefficient for dedicated calculation of refill data by at least 5% or when consensus about inclusion existed within the team of researchers supported by clinical evidence from literature.

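### The primary ANOVA prespecifies arm alone: department, the stratification factor, is not secured as a term, and possible correlation within group III sessions is not handled

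*Protocol article*

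**What the plan says.** Statistical Methods states the primary test and its predictor: "an analysis of variance test will be performed on the outcome measures for the three patient groups", and "The independent variable will be the three intervention groups". The quantity analysed is a change score: "we will compare the difference between the first and last time-point between groups". The same section has a rule for further terms: "In all analyses, potential confounders will be included if they independently changed the beta coefficient" by at least 5%, or when the research team agrees on inclusion with support from clinical literature. Department is not named there, and neither is session.

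Two features of the design bear on this model:

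- Assignment of Interventions: patients are randomised "stratified by department (eg, neurology, vascular surgery, and cardiology) in a 1:1:1 ratio into one of the three groups".
- Group and Individual Consultations (Group III): only group III receives "a single group consultation of 60 minutes led by a nurse and a pharmacist followed by two individual consultations". That section also presents the session as an occasion to meet peers, and the Discussion says that patients can talk about the need for adherence with peers.

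The Sample Size section mentions neither department nor sessions.

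**The concern.** The model as written does not reflect two features of the design, and the two omissions act in opposite directions.

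First, a stratification factor that predicts the outcome but is left out of the model leaves its variance in the error term. The estimate stays unbiased, but the standard error is too wide and the precision that stratification could buy is lost.

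Second, an ANOVA treats patients as independent. Patients who attend the same session share its leaders and its discussion. If session effects vary, the mean of group III varies more than the ANOVA assumes. The contrasts with group III then look more certain than they are. These contrasts matter: the Sample Size section expects group III to do best (85%), and the Intervention section gives the comparison of II with III as the reason for three arms.

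**Working it through.** **Inputs.** From the protocol article: three arms, 1:1:1, 200 per arm, SD 30 points for adherence at the start of the study, planned step of 10 points. Not in the article, so assumed: share of change-score variance explained by department (R²) 0.02-0.10; session size m 6-12; intraclass correlation (ICC) 0.01-0.05. The article gives no figure of its own on this point to reproduce.

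**Step 1: would the 5% rule bring department in?** Leaving out department shifts an arm contrast by (difference between the arms in a department's share) × (difference in mean change between departments). Five percent of the planned 10-point effect is 0.5 points. Even if two departments differed by a full 10 points, the shift reaches 0.5 only with an imbalance of 0.5/10 = 5 percentage points, that is 10 of 200 patients. Stratification is meant to prevent such an imbalance. If the observed arm effect is small, 5% of it is small too, and chance may bring department in. Either way, the data decide whether it is included.

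**Step 2: department left out.** Ratio of the unadjusted to the correct standard error = 1/√(1 − R²). Actual type I error at nominal 5% = 2[1 − Φ(1.96/√(1 − R²))].

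| R² | SE ratio | Type I error | Power for 10 points, without / with department |
|---|---|---|---|
| 0.02 | 1.01 | 4.8% | 91.7% / 92.0% |
| 0.10 | 1.05 | 3.9% | 92.6% / 94.0% |

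Power uses SD 30 and 200 per arm.

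**Step 3: sessions ignored, contrasts with group III.** Design effect in group III: DE = 1 + (m − 1) × ICC. Groups I and II have no session, so the ratio of the true to the assumed variance of a contrast is r = (1 + DE)/2. Type I error = 2[1 − Φ(1.96/√r)].

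| m | ICC | DE | √r | Type I error | Power with the correct SE |
|---|---|---|---|---|---|
| 6 | 0.01 | 1.05 | 1.012 | 5.3% | 90.9% |
| 10 | 0.02 | 1.18 | 1.044 | 6.1% | 89.1% |
| 10 | 0.05 | 1.45 | 1.107 | 7.7% | 85.4% |
| 12 | 0.05 | 1.55 | 1.129 | 8.3% | 83.9% |

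On the planning SD, the assumed standard error is 30 × √(2/200) = 3.00 points. In the last row it should be 30 × √(2.55/200) = 3.39 points. These are single contrasts at nominal 5%; Duncan's test is not modelled.

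**Step 4: both together, III against I.** Variance ratio = (1 − R²)(1 + DE)/2.

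- m = 8, ICC 0.02 (DE 1.14), R² 0.05: 0.95 × 2.14/2 = 1.017, type I error 5.2%.
- m = 10, ICC 0.05 (DE 1.45), R² 0.10: 0.90 × 2.45/2 = 1.103, type I error 6.2%.

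For the overall F test, simulation (20,000 runs each) gave 4.8% and 5.5% in these two cases. With sessions alone it gave 5.7% and 7.5%.

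**The case against.** **Other terms can enter.** A reader might infer from the sentence on the independent variable that the model is closed to everything but arm. It is not: the confounder rule applies to all analyses, and the team may add department by consensus. This stands, so the point is only that arm is the sole prespecified predictor. The rule still does not do the job. It looks for a shift in a coefficient, whereas the gain from department is precision, and no covariate rule represents correlation within a session.

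**This is detail for the analysis plan.** An article may leave covariates and error structure to a fuller document. That has weight for the session term, on which the article is silent. It has less for department, because the article states a model and a rule for adding terms, and together they tend to leave out the factor used for stratification.

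**The department effect is small.** This stands. The outcome covers two drug classes that, according to the Usual Care section, all participants should have, so differing drug regimens between departments are a poor argument. A change score also removes stable differences in level, so R² may be lower for change than for level.

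**Correlation within sessions is not shown.** This stands too. The exposure is one 60-minute session followed by individual consultations. The inflation arises only if session effects vary, or if similar patients attend together. A reader might infer that group III outcomes are known to be dependent and that type I error is in fact raised. The article gives no session size and no ICC, so it supports only the possibility.

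**The two effects offset each other.** They do in part, as Step 4 shows, so it would be wrong to say that the trial's standard errors are all too narrow, or all too wide. But the offset depends on unknown quantities, and it disappears once department enters the model.

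**Conclusion.** The point holds in a limited form. Arm is the only prespecified predictor, and the 5% rule does not secure the stratification factor. Leaving out department is conservative and costs little: standard errors about 1-5% too wide if R² for change is 0.02-0.10, and 0.3-1.4 percentage points of power on the planning figures. It does not endanger any conclusion.

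Possible correlation within group III sessions runs the other way and affects contrasts with group III; II against I involves no session. The type I error of about 5.3-8.3% is an illustration that rests wholly on the assumed m and ICC. At the low end it is negligible. The action is worth taking because it is cheap and because contrasts with group III carry the main questions of the trial.

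**What to change.** 1. State that department enters every between-arm model as a fixed factor, whatever the 5% rule gives. Cost: one sentence and two degrees of freedom out of about 600; the data are already held for randomisation.
2. Record for each group III patient which group session was attended. Cost: one data field. It should be recorded at the time, since it may be hard to recover later.
3. For contrasts with group III, fit a partially nested model (random session effect in group III only, patients in I and II treated as independent) or use cluster-robust standard errors, at least as a sensitivity analysis. With 200 patients and sessions of 6-12 there would be about 17-33 sessions (200/12 to 200/6), so a small-sample correction is advisable. Cost: slightly wider intervals for these contrasts. Over the assumed range, power for a 10-point difference stays at 83.9-90.9% with 200 per arm.

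Items 1 and 3 should be adopted together, because adding department alone removes the partial offset.

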## Methods

### Study Setting

Participants will be drawn from a hospital‐wide screening program. This screening program is situated at the cardiovascular outpatient clinics in an academic medical center in Nijmegen, the Netherlands. All new patients diagnosed in the last 6 months with acute coronary syndrome, peripheral arterial disease, an aneurysm of the aorta, or stroke/transient ischemic attack (TIA) and referred to the departments of vascular surgery, neurology, or cardiology are automatically included in this program.

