### Eligibility Criteria

From this population, participants aged 18 years and older will be selected based on the following inclusion criteria: presence of CVD (acute coronary syndrome, peripheral arterial disease, an aneurysm of the aorta, or stroke/TIA), diagnosed in the last 6 months by a medical specialist, willingness to remain in follow‐up for a period of one year, and provision of signed informed consent. Exclusion criteria are pregnancy (reported by the patient), severe comorbidity (eg, a mental health diagnosis considered by a physician to be a contraindication), problems with the Dutch language (reported by the nurse), or logistic problems such as lack of computer access.

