### Sample Size

This study is mainly powered on the primary outcome, the detection of a significant difference between the three degrees of care (usual, additional website, additional counseling) on medication adherence as determined by refill records of computerized pharmacy systems. Based on previous research in our population and data from the literature [26], we estimate that the adherence at the start of the study will be 65% in each group with a standard deviation (SD) of 30%. We hypothesize that the intervention given in group II and the intervention given in group III will result in an increase of 10% in adherence to treatment, resulting in mean adherence rates of 75% and 85% in groups II and III, respectively. To detect these differences in medication adherence the estimated group size with a power of 80% and an alpha of .05 (2‐sided) would be 200 in each group, resulting in 600 participants in total.

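### The primary comparison uses raw change in refill adherence, whose first value may be missing or unstable for new starters and whose spread is not the SD of 30 used for planning; adjusting the follow-up level for baseline avoids both problems

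*Protocol article*

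**What the plan says.** The Statistical Methods section of the protocol article states that "an analysis of variance test will be performed on the outcome measures for the three patient groups", and then narrows this: "we will compare the difference between the first and last time-point between groups for the primary and secondary outcomes measures". Multiplicity is handled in the next step: "To correct for multiple comparison, a Duncan’s multiple range test will be performed". Baseline adherence is not named as a covariate. The only adjustment clause admits confounders by a 5% change in the coefficient or by team consensus.

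The Primary Outcome section defines refill adherence for platelet inhibitors and lipid-modifying drugs. It is the theoretical duration of supply divided by the time from the start date to the last fill. Records reach back 3 years before the event. The section does not say which stretch of refills forms the first time-point.

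Patients are recent cases. The Study Setting section describes them as "All new patients diagnosed in the last 6 months with acute coronary syndrome, peripheral arterial disease" and other vascular diagnoses, and the Eligibility Criteria section requires disease "diagnosed in the last 6 months by a medical specialist".

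The Sample Size section assumes that "the adherence at the start of the study will be 65% in each group with a standard deviation (SD) of 30" percent, with an intervention effect "resulting in mean adherence rates of 75% and 85% in groups II and III, respectively". It arrives at 200 per group for 80% power at a two-sided alpha of .05.

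**The concern.** Two separate things go wrong when the primary variable is last minus first.

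The first is whether the starting value exists. The Usual Care section says that all participants should be on antiplatelet and lipid-lowering therapy, so people who begin these drugs at diagnosis are an expected part of the sample. Someone with one fill before randomisation has no interval between start and last fill, and the ratio cannot be computed. With two or three fills it can be computed but is unstable. The change score of such a patient is either missing or has to be built on an imputed value for a quantity that never existed, although the plan promises an intention-to-treat analysis.

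The second is precision. The SD of 30 is the spread of adherence at one time. A difference of two measurements has its own SD, which depends on how strongly they correlate, and the article gives neither that SD nor the correlation.

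At stake is mainly the comparison of neighbouring groups. The Intervention section makes website versus website plus consultations a motive for having three arms.

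**Working it through.** **Inputs.** From the Sample Size section: SD 30, means 65 / 75 / 85 (10 points between neighbours, 20 between I and III), 200 per group, two-sided alpha .05. The correlation ρ between first and last adherence is not in the article, so a range is used. Equal SDs of 30 at both times are also assumed.

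**The plan's own figure.** For two means, n = 2 × (SD/difference)² × (1.960 + 0.842)² = 2 × 9 × 7.85 = 141.3, so 142 per group. The stated inputs therefore give 142, not 200. The surplus is not explained, but it acts as a reserve here: at SD 30 and 200 per group, power for 10 points is about 91%.

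**When the first value exists.** Adherence = days supplied ÷ (last fill date − start date).
- One fill: the denominator is 0, so the ratio is undefined.
- Few fills, illustrated with assumed 90-day fills collected exactly on time and the last fill's supply counted (the article does not exclude it): two fills give 180/90 = 200%; five fills give 450/360 = 125%. A fully adherent patient would show a fall of 75 points that comes from the formula alone. Randomisation spreads this evenly over the arms, so it adds noise rather than bias.

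**Spread and power.** SD of change = 30 × √(2(1 − ρ)). Residual SD with baseline as covariate = 30 × √(1 − ρ²). Power is from the noncentral t distribution, 200 per group, 10 points, alpha .05 unadjusted. That level suits neighbouring means, which Duncan's test compares at the nominal 5%.

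| ρ (assumed) | SD of change | Power, change | Residual SD, ANCOVA | Power, ANCOVA |
|---|---|---|---|---|
| 0 | 42.4 | 65% | 30.0 | 91% |
| 0.3 | 35.5 | 80% | 28.6 | 94% |
| 0.5 | 30.0 | 91% | 26.0 | 97% |
| 0.6 | 26.8 | 96% | 24.0 | 99% |

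The two SDs satisfy (SD of change)² ÷ (residual SD)² = 2(1 − ρ)/(1 − ρ²) = 2/(1 + ρ). Change scores thus need 2.0, 1.54, 1.33 and 1.25 times as many patients as ANCOVA for the same power at these four values.

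**Where 80% is lost.** With 200 per group, 80% power needs SD ≤ 10 ÷ (2.802 × √(2/200)) = 35.7. Solving 30 × √(2(1 − ρ)) = 35.7 gives ρ ≈ 0.29. With a Bonferroni correction for three comparisons the break-even is ρ ≈ 0.47.

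**Other contrasts at the worst case, ρ = 0 (SD 42.4).** The overall F test for 65 / 75 / 85 has noncentrality 200 × (10² + 0² + 10²)/42.4² ≈ 22, and power about 99%. The 20-point contrast of III versus I has power above 99%.

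**The case against.** The case for leaving the plan alone has real force.

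- A reader might infer that many participants have no baseline. The article does not show this. It gives no proportion. The 3-year look-back gives earlier users a history, and patients up to 6 months past diagnosis can have several fills before inclusion. The Sample Size section takes a starting value of 65% partly from previous research in the same population. What stands is narrower: the baseline window is not defined, and the value may be absent or unstable for those who started at diagnosis.
- A reader might infer that the trial is underpowered. That does not follow either. A correlation of 0.5 is where the two SDs are equal, not where power fails. With complete baselines, 200 per group holds 80% for neighbouring groups down to about 0.29, and the overall test is safe throughout.
- A reader might assume that new starters would be dropped and compute the power lost. The article plans intention-to-treat and multiple imputation, not exclusion. The difficulty is what an imputed baseline would mean for someone with no earlier supply.
- Change scores are unbiased under randomisation where a baseline exists, and the Recruitment section states an interest in how adherence develops over time. Both points stand. They make this a matter of efficiency and completeness, not validity, and within-person change can still be described.
- An exact refill window may be left to a fuller document. That is fair, but the choice of raw change as the tested quantity is stated in the article itself.

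**Conclusion.** The point holds as a should-fix. The stated analysis tests a quantity that the article's own formula cannot deliver for a patient with a single earlier fill, and its spread is not the one used for planning. For neighbouring groups, power ranges from about 65% (ρ = 0) through 80% (ρ = 0.3) and 91% (ρ = 0.5) to 96% (ρ = 0.6). Adjusting the follow-up level for baseline keeps it at 91% or more in every case. The overall three-group test and III versus I are little affected.

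This rests on equal SDs of 30 at both times, on an assumed range for ρ, and on an unadjusted 5% level. The power figures for change also take every baseline as available. The number of patients without a usable baseline cannot be estimated from the article, so no loss is put on it.

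**What to change.** State the primary analysis as follows: the refill adherence level over the 12 months after randomisation, compared between the three groups by analysis of covariance, adjusted for pre-randomisation refill adherence where it exists. For patients without usable earlier supply, set that covariate to a constant and add an indicator for no prior supply. Because this status is fixed before randomisation, the indicator does not bias the comparison of arms, and nobody is lost or given an imputed baseline for want of one. Define the refill window for the baseline value and the minimum number of fills it needs.

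Treat the continuous secondary outcomes (LDL cholesterol, systolic pressure, the Modified Morisky score) the same way: the 12-month value adjusted for the baseline value.

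The data are already to be collected and the sample size need not change. The cost is that the primary analysis variable is restated, which should be done and recorded before the data are analysed, and that within-person change becomes descriptive.

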### Secondary Outcomes

All secondary outcome measurements will be obtained just before inclusion (in the usual care screenings program) and one year after inclusion. The secondary outcome measurements include clinical responses to drug therapy (eg, cholesterol level), self-report questionnaires, and changes in systolic blood pressure.

Clinical responses to drug therapy will be recorded. A recorded low-density lipoprotein cholesterol level above 20% of preestimated low-density lipoprotein cholesterol reduction during follow-up will be considered as possible indication of poor adherence. If the patient also uses antihypertension drugs, the blood pressure on baseline will be compared to blood pressure after one year and will need to be within target blood pressure for cardiovascular risk management (systolic <135 mm Hg). These office blood pressure measurements are performed according to the recommendations of the European Society of Hypertension [15] with a validated automated device; data will be based on a mean of four office measurements.

Second, two validated self-report questionnaires will be used. The MMS will be used to measure adherence [17]. Each of the 8 items measures a specific medication‐taking behavior. MMS scores can range from 0 to 8 and can be classified into three levels of adherence: low adherence (score of less than 6), medium adherence (score of 6 to less than 8) and high adherence (score of 8) [31]. The BMQ will be used to provide information about the beliefs, perceived necessity, and concerns patients have regarding their illness and prescribed medication [18]. Respondents indicate their degree of agreement with each individual statement about medicines on a 5‐point Likert scale. It is then possible to differentiate between patients on the basis of their beliefs about the necessity of their medication and their concerns about taking it. Patients can be classified into four different categories: accepting (high necessity and low concerns), ambivalent (high necessity and high concerns), skeptical (high concerns and low necessity), and indifferent (low concerns and low necessity) [32,33].

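### First-to-last differences under ANOVA waste baseline information for the numeric secondary outcomes, and do not work for the LDL flag or the BMQ types

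*Protocol article*

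**What the plan says.** The Statistical Methods section of the protocol article states that "an analysis of variance test will be performed on the outcome measures for the three patient groups". It then names what is analysed: "The dependent variable is medication adherence measured with the dedicated calculation of refill data". The next sentence extends the comparison to the secondary outcomes: "we will compare the difference between the first and last time-point between groups for the primary and secondary outcomes measures". No other method for comparing the three arms on a secondary outcome appears. The logistic regression in that section is for determinants of low refill adherence, and the normality check serves the associations between parameters.

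The Secondary Outcomes section lists the outcomes as "clinical responses to drug therapy (eg, cholesterol level), self-report questionnaires, and changes in systolic blood pressure", measured just before inclusion and at one year. It then adds categorical readings:

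- **LDL cholesterol:** a result judged against the predicted reduction "during follow-up will be considered as possible indication of poor adherence".
- **Blood pressure:** in users of antihypertensives, baseline is compared with one year, and the pressure "will need to be within target blood pressure for cardiovascular risk management" (systolic below 135 mm Hg).
- **MMS:** a score from 0 to 8, with three ordered levels available.
- **BMQ:** 5-point Likert items on necessity and concerns. "Patients can be classified into four different categories", which are accepting, ambivalent, skeptical and indifferent.

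The section does not say whether the score or the category is the analysed form.

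**The concern.** One contrast is stated for a set of outcomes of different kinds, which raises two separate issues.

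First, where the outcome is a number, a change score is a legitimate choice but rarely the most precise one. Part of a patient's change is regression from a chance high or low baseline, and the change score keeps that as noise. A model that adjusts for baseline removes it, using data the trial already has.

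Second, where the outcome is read as a category, a first-to-last difference needs a value at both times and a scale on which subtraction means something. The LDL flag lacks the first and the BMQ types lack the second.

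At stake are the precision of the secondary comparisons that accompany the refill result, and the risk that the form of an outcome, or the numbering of its categories, is settled only once the data are in hand.

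**Working it through.** The documents give no power or variance figure for any secondary outcome, so there is no figure of the plan's own to reproduce. The inputs below are assumptions, except the 200 per group, which is in the Sample Size section.

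**1. Numeric outcomes: change score against baseline adjustment.** Let SD be the standard deviation, equal at both visits, and r the correlation between baseline and one year.

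- Variance of the change score: 2(1 − r)SD².
- Residual variance after adjusting for baseline: (1 − r²)SD².
- Ratio: (1 − r²) / [2(1 − r)] = (1 + r)/2.

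| Assumed r | Ratio | Reduction in variance |
|---|---|---|
| 0.3 | 0.65 | 35% |
| 0.5 | 0.75 | 25% |
| 0.7 | 0.85 | 15% |

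The ratio is below 1 for every r below 1, so adjustment does not lose on this count.

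**2. What this means for power, using systolic pressure.** Assumed: baseline mean 140 mm Hg, SD 16, r = 0.5, one-year means 135, 135 and 130.5 in groups I, II and III, 200 per arm, alpha 0.05.

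- Grand mean at one year: (135 + 135 + 130.5)/3 = 133.5. The deviations are 1.5, 1.5 and −3, and their squares sum to 2.25 + 2.25 + 9 = 13.5.
- Change-score variance: 2 × 0.5 × 16² = 256. Noncentrality: 200 × 13.5/256 = 10.55. Three-group F test: power 84%.
- Adjusted variance: 0.75 × 16² = 192. Noncentrality: 200 × 13.5/192 = 14.06. Power 93%.

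Simulation of 1,500 trials under the same assumptions gave the same two figures, 84% and 93%.

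The Secondary Outcomes section ties the blood-pressure comparison to users of antihypertensives, and their number is not given. If only 100 per arm qualified (assumed), the noncentralities halve to 5.27 and 7.03, and power is about 52% against 65%. The variance ratio does not change.

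**3. LDL flag.** It is defined by the reduction seen during follow-up. Before inclusion no such reduction exists, so the flag has a last value and no first value, and the stated difference cannot be computed. The LDL level itself is measured at both times and has no such problem.

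**4. BMQ types.** Number them accepting 1, ambivalent 2, skeptical 3, indifferent 4. A move from ambivalent to accepting scores 1 − 2 = −1, and from indifferent to accepting 1 − 4 = −3. Swap the numbers of ambivalent and indifferent and the same two moves score −3 and −1. Nothing in the questionnaire favours either numbering, so a difference between types carries no information of its own. The necessity and concerns scores are unaffected.

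**5. On-target blood pressure.** Status exists at both times, so the change is −1, 0 or +1, and its mean is a change in proportion. In 10,000 simulated null trials with 200 per arm, ANOVA of the change in a yes/no variable rejected in 5.2% at a nominal 5%. The test is valid. What it loses is the distance of each reading from the threshold.

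**The case against.** The strongest reply is that the plan does not prescribe an analysis of the categories. The listed outcomes are in measured form, the BMQ and MMS classes are only optional, the LDL flag is called a possible indication, and Statistical Methods names refill adherence as the dependent variable. The same section also reports BMQ results "in descriptions of observed effects (eg, change in BMQ, determinants for adherence, evaluation of the use of iVAZ, and appreciation of nurse intervention". On that reading every secondary outcome has a numeric score, and a change-score ANOVA of it is valid.

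Most of this stands. A reader might infer that the plan orders an ANOVA of numbered BMQ types, but no sentence says so. A reader might also infer that the secondary outcomes would be uninterpretable, or that ANOVA of a yes/no change is invalid. The documents do not support the first, because numeric scores exist throughout, and the null simulation contradicts the second. No power is claimed for the secondary outcomes either, since the Sample Size section says the study is mainly powered on the primary outcome.

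Two things remain. The sentence that sets the contrast covers the secondary outcomes without exception, and for the LDL flag and the BMQ types that contrast is unavailable or empty. And on the favourable, wholly numeric reading, the stated change-score analysis is still the less precise one.

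It can also be said that the choice of form for each outcome belongs in a full protocol or analysis plan that is not shown. That is fair as to missing detail, and no omission is held against the article here. The point concerns the contrast that the article does state.

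**Conclusion.** The point holds in limited form.

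- **Numeric secondary outcomes:** the stated analysis is valid but inefficient. Baseline adjustment lowers the residual variance by 25% at r = 0.5, and by 15% to 35% for r from 0.7 to 0.3, given equal variances at both visits. In the assumed systolic example, power is about 93% against 84% with 200 per arm. The variance ratio depends only on r and the equal variances. The power figures also depend on the assumed means, SD and number of patients, and fall if only users of antihypertensives count.
- **LDL flag:** the stated difference does not exist.
- **BMQ types:** the stated difference has no meaning, if they are analysed as types.
- **On-target blood pressure:** the stated difference is valid, with lost information.

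The primary outcome and the sample size are not affected by this point.

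**What to change.** In Statistical Methods, replace the single first-to-last sentence, as far as it covers secondary outcomes, with the following:

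- Systolic pressure, LDL level, MMS score (0 to 8), BMQ necessity score and BMQ concerns score: the one-year value in a linear model with arm and the baseline value.
- LDL flag: the proportion flagged at follow-up compared between arms by logistic regression, with no baseline status because none exists.
- On-target blood pressure: status at one year by logistic regression with arm and baseline status.
- BMQ types: a cross-table by arm, or a nominal-category (multinomial) model, and no differences of codes.

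State for each outcome that has both a score and a category which of the two is the analysed form, so that the Secondary Outcomes and Statistical Methods sections agree. The cost is analysis wording only: the scores are already measured before inclusion and at one year, and no visit, measurement or patient is added.
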